3	Alternative composite threshold: ≥100 m absolute MWD gain	Tests sensitivity to an absolute rather than relative distance criterion
4	Functional improvement component only (no revascularization criterion)	Isolates the predictive relationship with functional adaptation. Mandatory pre-specified secondary analysis; reported in all primary publications regardless of composite outcome result.
5	Revascularisation-free survival component only	Isolates the predictive relationship with intervention requirement. Mandatory pre-specified secondary analysis; reported in all primary publications regardless of composite outcome result.
6	Restriction to guideline-concordant revascularisation events only	Removes patient-preference-driven events to reduce confounding; specifically examines discordant cases (functional improvement achieved but revascularisation occurred)
7a	Four-predictor model: muscle density, VAT, age, sex (excluding baseline MWD)	Robustness check with an EPV approximately 10; tests stability of primary model estimates when baseline MWD is excluded
7b	Three-predictor model (muscle density, VAT, age; excluding sex)	Robustness check with an EPV approximately 13–14
8	Alternative muscle density threshold: 33 HU	Tests lower threshold sensitivity for myosteatosis classification (Martin et al. [21] value for BMI ≥ 25 kg/m^2^); see also Section 2.6
9	Alternative muscle density threshold: 41 HU [Martin et al. [21], BMI < 25 kg/m^2^ stratum]	Tests higher threshold sensitivity for myosteatosis classification; see Section 2.6
10	Alternative VAT threshold: --20 cm^2^ (110 cm^2^ M; 80 cm^2^ F)**†**	Tests sensitivity to a more conservative VAT threshold
11	Alternative VAT threshold: +20 cm^2^ (150 cm^2^ M; 120 cm^2^ F)**†**	Tests sensitivity to a more stringent VAT threshold
12	Adherent subgroup (≥30/36 sessions completed)	Per-protocol analysis to assess treatment-specific effects
13	30% treatment failure rate scenario (approximately 30 failures)	Reports model performance and power under a more optimistic clinical assumption
14	Expanded confounding model: primary five predictors plus ABI, smoking status, diabetes, Clinical Frailty Scale score, TASC II classification, SMI, SAT	Pre-specified secondary expanded model; EPV approximately 3–4 (acknowledged limitation); designated as robustness sensitivity analysis; tests whether primary predictor associations are independent of additional clinical confounders

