### Sample size

Sample size is determined primarily by the precision required for the primary model’s discrimination statistic [26, 27]. A minimum of 40 treatment failures is targeted for the five-predictor primary logistic regression model (muscle density, VAT area, age, sex, baseline MWD), yielding an events per variable (EPV) ratio of approximately 8. This EPV is recognized as modest, providing the primary rationale for the conservative four-predictor robustness check (Table 3, sensitivity analysis #7a). A supplementary power calculation confirms approximately 80% power to detect an odds ratio ≥2.0 per 10 HU decrease in skeletal muscle density (α ═ 0.05, two-tailed).

Assuming a treatment failure rate of 40%, reflecting the program non-completion component of the 40–50% failure rate reported in real-world European SET series [9] and a local institutional audit (approximately 38%); this 40% assumption captures both program non-completion and early revascularization combined, without separately modeling the functional non-response rate among completers. Accounting for 22% attrition from dropout and protocol non-completion, 128 patients must be enrolled to achieve 100 evaluable participants with 40 treatment failures. The IRONIC trial [8], which demonstrated that a significant proportion of claudicants managed conservatively required revascularization during follow-up, supports the clinical relevance of this failure rate, although it was not designed to quantify SET-specific non-response. A pre-specified sensitivity analysis reports model performance under a 30% failure rate scenario (approximately 30 failures, approximately 70% power). All precision-related conclusions are explicitly framed within the derivation cohort boundaries; external validation is necessary before any clinical translation.

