### Statistical analysis

**Analytical hierarchy:** In all primary analyses (H1 and H2), skeletal muscle density and VAT area are treated as continuous standardized z-scores (mean = 0, SD = 1). This approach serves as the foundation for all inferential conclusions. All classification thresholds—whether derived from cohorts via Youden index maximization (cutpointr) or from literature pertaining to non-PAD populations (Martin et al. [21]; general population VAT reference values [23, 24])—are established post-hoc and are explicitly designated as exploratory and hypothesis-generating. These thresholds do not influence the primary predictive model and necessitate external validation in an independent PAD cohort prior to any clinical application. This distinction is consistently maintained throughout the statistical analysis section.

All analyses are conducted using International Business Machines (IBM) Statistical Package for the Social Sciences (SPSS) Statistics, version 30 (IBM Corp., Armonk, NY) and R version 4.3 (R Foundation for Statistical Computing, Vienna, Austria; packages: rms, cmprsk, mice, boot, cutpointr, survminer). The complete statistical analysis plan is pre-registered at ClinicalTrials.gov before database lock, and no post-hoc modifications to the primary analysis are allowed.

**Primary model specification:** The primary model for H1 and H2 is a pre-specified multivariable logistic regression with binary treatment success (success/failure) as the outcome, incorporating five predictors: skeletal muscle density (continuous standardized z-score), VAT area (continuous standardized z-score), age (continuous), sex (binary), and baseline MWD (continuous). SMI and SAT are excluded from the primary model; they are included only as covariates in the pre-specified secondary expanded model. This model specification is fixed and will not be altered once data collection begins.

The two co-primary hypotheses (H1, H2) are tested at a Bonferroni-corrected significance threshold of p < 0.025 per hypothesis (family-wise α ═ 0.05). Hypothesis 3 (H3), pertaining to sarcopenic obesity, is classified as a secondary/descriptive hypothesis and is not subject to family-wise correction. Secondary Spearman correlation analyses between continuous body composition parameters and secondary functional outcomes will be reported with Benjamini-Hochberg false discovery rate correction (q < 0.05).

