**Continuous predictor modeling**: In the primary model, skeletal muscle density and VAT area are utilized as continuous standardized z-scores. The nonlinearity of each continuous predictor is assessed using restricted cubic splines, with three to five knots selected based on the Akaike Information Criterion. Exploratory cutpoint derivation employing the Youden index (implemented via cutpointr) is conducted as a separate secondary exploratory analysis and is clearly labeled as hypothesis-generating; derived thresholds are not employed in the primary predictive model.

Internal validation is performed using bootstrap resampling (1000 samples), yielding optimism-corrected area under the curve (AUC), calibration slope, and calibration-in-the-large. The bootstrap resampling procedure encompasses the entire analytical pipeline, including nonlinearity assessment (spline knot selection); the same bootstrap samples are utilized for optimism correction across the full pipeline. For any exploratory cutpoint derivation, the derivation step is nested within a distinct independent bootstrap loop to prevent double-counting of optimism. A four-predictor model excluding baseline MWD (skeletal muscle density, VAT area, age, sex; EPV approximately 10) is included as a pre-specified robustness check (Table 3, sensitivity analysis #7a). A three-predictor model excluding sex (EPV approximately 13–14) is also part of the pre-specified robustness checks. For H3, the four-group sarcopenic obesity classification is incorporated as a categorical predictor in a similar model; H3 analyses are reported descriptively and interpreted as exploratory.

**Pre-specified secondary expanded model:** A secondary expanded confounding model is pre-specified, adjusting for the five primary predictors along with additional variables: ABI (continuous), smoking status (categorical), diabetes mellitus (binary), Clinical Frailty Scale score (ordinal), TASC II classification (categorical), SMI (continuous standardized z-score), and SAT area (continuous standardized z-score). This expanded model comprises approximately 12 predictors and, with 40 expected events, yields an EPV of approximately 3–4; this EPV limitation designates the expanded model as a robustness sensitivity analysis rather than a primary inferential tool (Table 3, sensitivity analysis #14). Results will be reported with 95% confidence intervals and interpreted cautiously due to limited EPV.

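### The expanded confounding model (Table 3, #14) is sized in variables rather than parameters: at 40 events its EPV is about 2.7–2.9 under ordinary coding, and an unpenalised fit could mask the attenuation it looks for

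*Protocol article*

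**What the plan says.** The Statistical analysis section builds the expanded model from the five primary predictors, "skeletal muscle density (continuous standardized z-score), VAT area (continuous standardized z-score), age (continuous), sex (binary), and baseline MWD (continuous", and seven additions. The first five additions are "ABI (continuous), smoking status (categorical), diabetes mellitus (binary), Clinical Frailty Scale score (ordinal), TASC II classification (categorical"; SMI and SAT area follow as standardised continuous terms. The size is then given: "This expanded model comprises approximately 12 predictors and, with 40 expected events, yields an EPV of approximately 3–4".

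Table 3, #14 repeats the figure with a caveat, "EPV approximately 3–4 (acknowledged limitation); designated as robustness sensitivity analysis", and gives the model its purpose: it "tests whether primary predictor associations are independent of additional clinical confounders". The events come from the Sample size section: "128 patients must be enrolled to achieve 100 evaluable participants with 40 treatment failures".

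The article gives no number of levels for smoking or TASC II, does not say how the frailty score enters, and names no estimator for #14. The primary model is described as multivariable logistic regression, with no penalty mentioned.

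**The concern.** A factor with k levels uses k − 1 regression parameters, and it is parameters that drive small-sample behaviour. Counting variables is harmless in the primary and reduced models, where each term has one parameter (splines aside). It is not harmless in #14, which adds two categorical variables and an ordinal one.

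The understatement matters because of what #14 is for. Maximum-likelihood logistic estimates move away from zero as EPV falls, and more so in the expanded model than in the five-predictor model it will be compared with. Confounding of the kind usually feared would show as a fall in the CT odds ratios from the primary to the expanded model. Small-sample inflation pushes the other way, so stable or larger odds ratios could be taken for independence when part of the stability is an artefact. Wide intervals and cautious wording address imprecision, not a bias with a direction. #14 is the only listed analysis that adjusts for ABI, smoking, diabetes, TASC II, SMI and SAT.

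**Working it through.** **Inputs from the article.** 40 expected failures, 100 evaluable, 128 enrolled, a 40% failure rate and a 30-failure scenario (Sample size); five primary predictors and seven added covariates (Statistical analysis).

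**Assumptions.** Smoking has two or three levels. TASC II has four classes unless collapsed. Frailty is one linear term, or a factor with 3–8 contrasts.

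**The plan's figure.** 5 + 7 = 12 variables, and 40/12 = 3.33, inside the stated 3–4. The other stated EPVs use the same convention and also reproduce: 40/5 = 8, 40/4 = 10, 40/3 = 13.3. An EPV of 4 would need 40/4 = 10 parameters, fewer than the 12 variables named.

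**Counting parameters.** Nine terms take one parameter each: the five primary predictors, ABI, diabetes, SMI and SAT. To these add smoking, TASC II and frailty, in that order below.

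| Coding | Parameters | EPV at 40 events |
|---|---|---|
| All single-parameter | 9 + 1 + 1 + 1 = 12 | 3.33 |
| Smoking 3 levels, TASC II 2 groups, frailty linear | 9 + 2 + 1 + 1 = 13 | 3.08 |
| Smoking 3, TASC II 3, frailty linear | 9 + 2 + 2 + 1 = 14 | 2.86 |
| Smoking 2, TASC II 4, frailty linear | 9 + 1 + 3 + 1 = 14 | 2.86 |
| Smoking 3, TASC II 4, frailty linear | 9 + 2 + 3 + 1 = 15 | 2.67 |
| As above, frailty with 3–8 contrasts | 17–22 | 2.35–1.82 |

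An EPV of 3 at 40 events allows at most 13 parameters, so at least one of the two categorical variables must be reduced to two groups. If TASC II keeps four classes, even two-level smoking leaves 14.

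**Varying the events at 15 parameters.** 30/15 = 2.0; 45/15 = 3.0; all 128 analysed at 40% gives 128 × 0.40 ≈ 51 events and 51/15 = 3.4.

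**Effect on the estimates.** Simulation with 2,500 replicates per setting and unpenalised maximum likelihood. The true density odds ratio was set at 2.0 per SD and the true VAT log odds ratio at about 0.40. Effects, correlations and level distributions are all assumed; the article's own effect size is per 10 HU, with no SD given.

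- N = 100, 40% failures, 15 parameters: mean log odds ratios too large by about 26–27% (density) and 27–34% (VAT). In the five-predictor model: 8–9% and 10–14%.
- N = 128, about 51 events, 15 parameters: about 15–20%, against 4–9% in the five-predictor model.
- Frailty as a factor (18 parameters, N = 100, 40% failures): about 33–40%, with 22–39% of fits failing or separating.
- True confounding that should shrink the density log odds ratio by 13% (true expanded-to-primary ratio 0.706/0.813 = 0.87): at N = 100 and 15 parameters the fitted ratio was 0.899/0.874 = 1.03, and in about 51% of replicates the expanded estimate was at least as large as the primary one. At N = 128 the fitted ratio was 0.97 against a true 0.86, so masking was partial.
- In the same confounded setting at N = 100, Firth fits of the 15-parameter model averaged 1.00 (density) and 1.05 (VAT) times the truth.
- The SD of the density log odds ratio there was 0.57 in the expanded model and 0.34 in the five-predictor model.

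**The case against.** The case on the other side has real force.

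- **The division is right.** 40/12 is 3.33. A reader might infer a calculation error; the fault lies in the unit counted. This stands.
- **No single EPV follows from the article.** A reader might infer that the true figure is 2.7 or lower. That needs level counts the article does not give: 2.9 is equally consistent with its labels, and collapsing TASC II gives 3.1. The event count may also exceed 40. The article calls 40 a minimum, says the 40% rate does not separately model non-response among completers, and keeps non-adherers in the primary analysis. At 15 parameters, 45 events would give 3.0. This stands as a limit on the claim, but the stated EPV is itself tied to 40 events, and a categorical label set beside a binary one points to more than two levels.
- **The limitation is disclosed.** Table 3 and the text acknowledge low EPV and demote the model. The Discussion concedes that residual confounding by disease extent cannot be excluded. A reader might infer that the H1 and H2 conclusions rest on #14. They do not: both are tested in the five-predictor model, which the article makes the basis of inference. What the disclosure omits is the direction of the bias.
- **The estimator is inferred.** No fitting method is named for #14, and a fuller analysis plan may supply one. The bias claim is therefore conditional on ordinary maximum likelihood.
- **Masking is a tendency.** A reader might infer that #14 will hide confounding. The size depends on assumed effects and correlations, and imprecision is at least as large a problem.
- **Firth fitting does not isolate confounding.** Odds ratios are non-collapsible, so adding prognostic covariates can move them without any confounding. Profile-penalised-likelihood intervals also do not pool directly by Rubin's rules over the 20 imputations. Both stand and shape the fix.

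**Conclusion.** The point holds in a limited form. Model #14 is sized in variables. In parameters, at the plan's 40 events, with multi-level smoking and TASC II and a linear frailty term, it has about 14–15 and an EPV of about 2.7–2.9, not 3–4. It is lower with frailty as a factor, and 2.0 at 30 failures and 15 parameters. It reaches 3 or more only with coarser coding, chiefly TASC II in two groups, or with more events than stated.

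If #14 is fitted by ordinary maximum likelihood, the density and VAT log odds ratios tend to be inflated by roughly 20–30%, against about 10% in the five-predictor model, which can mask the attenuation #14 is there to detect. These percentages rest on assumed effects, correlations and level distributions. The matter concerns a disclosed, secondary robustness analysis; the tests of H1 and H2 and the sample size are untouched. It is worth correcting because it bears on the one analysis meant to show independence from these confounders, and the correction is cheap.

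**What to change.** In the Statistical analysis section and Table 3, #14:

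1. State model size and EPV in parameters, and fix the coding of smoking, TASC II and the Clinical Frailty Scale. For example, with smoking at three levels, TASC II at four classes and frailty linear: about 15 parameters, EPV about 2.7 at 40 events.
2. Fit #14 by Firth-penalised logistic regression, and refit the five-predictor model the same way as its comparator.
3. Name an interval method that works with the imputation: penalised estimates and standard errors pooled by Rubin's rules, or a method that combines the penalised likelihood profiles across the imputed data sets.
4. Describe the comparison as free of most small-sample inflation, and note that odds ratios may still shift through non-collapsibility.

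Leave the primary model as specified. The cost is a less favourable EPV, smaller odds ratios in #14 and a little extra analysis work in R, which the plan already uses. No new data or patients are needed, and enrolment is not planned to begin until June 2026.

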## Introduction

Peripheral arterial disease (PAD) affects approximately 236 million individuals aged 25 years and older, with intermittent claudication being its most common symptomatic manifestation [1]. International clinical practice guidelines, including the 2024 American College of Cardiology/American Heart Association (ACC/AHA), 2024 European Society of Cardiology (ESC), and 2024 European Society for Vascular Surgery (ESVS) guidelines, unanimously endorse supervised exercise therapy (SET) as the first-line treatment for intermittent claudication [2–4]. Furthermore, the 2024 ESC and ESVS guidelines specify that revascularization should be deferred until conservative management has been adequately trialed [3, 4]. A Cochrane systematic review demonstrates that exercise significantly enhances maximum walking distance and functional performance compared to no exercise [5]. Additionally, a second Cochrane review confirms the superiority of SET over home-based exercise and walking advice alone [6]. A meta-analysis of 15 randomized controlled trials shows significant improvements in physical health-related quality of life and perceived walking ability with structured exercise programs, although mental health component scores were not significantly affected [7].

Despite these benefits at the population level, individual treatment responses exhibit considerable heterogeneity. In the Invasive Revascularization or Not in Intermittent Claudication (IRONIC) study, 25% of conservatively managed patients ultimately required revascularization over five years, despite achieving comparable long-term outcomes to the revascularization group. This underscores both the tolerability of conservative management and the existence of a subgroup with insufficient response [8]. Real-world SET series report non-completion rates of 40–50% [9]. Conventional clinical predictors — including ankle-brachial index (ABI), age, sex, and disease severity — do not reliably forecast the extent of functional improvement achieved with SET [10]. However, patients with lower baseline walking capacity may derive proportionally greater benefits [10]. Currently, no validated metabolic tool exists to identify, prior to therapy initiation, patients lacking the biological substrate for aerobic adaptation, making them unlikely to benefit from a sustained exercise program.

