The composite endpoint comprises four pre-specified outcome combinations, addressed as follows: The primary analysis of treatment failure includes three specific scenarios: (i) program non-completion, defined as failure to attend the requisite number of SET sessions, regardless of functional outcome; (ii) functional non-response among program completers, characterized by completion of the program without achieving the MWD threshold at three months (T1); and (iii) revascularization occurring within the three-month follow-up period, irrespective of functional outcome. This approach aligns with the protocol’s objective of identifying patients capable of deriving sufficient benefit from conservative management alone. The rationale for classifying revascularization as treatment failure, even when accompanied by functional improvement, is that such cases indicate the conservative management pathway was not maintained. Sensitivity analysis #6 (Table 3) examines the subset of guideline-concordant revascularization events separately.

The four pre-specified outcome combinations are: (1) functional improvement achieved AND revascularization-free = treatment success; (2) functional improvement not achieved AND revascularization occurred = treatment failure; (3) functional improvement achieved BUT revascularization occurred = classified as treatment failure in the primary analysis; this discordant case type (functional improvement with revascularization) will be specifically examined in sensitivity analysis #6 (Table 3), restricting to guideline-concordant revascularization events only, to assess whether revascularization was guideline-concordant or driven by patient preference; (4) functional improvement not achieved AND revascularization-free = treatment failure. Failure to meet either criterion (b) or the MWD threshold in (a) constitutes treatment failure.

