**Multiple imputation specification**: Missing data are addressed through multiple imputation by chained equations (MICE). All analysis variables—including the primary composite outcome, all five primary predictors, all covariates in the expanded model, and secondary outcomes—are incorporated into the MICE model. Twenty imputation datasets are generated (50 iterations per dataset), and estimates are pooled according to Rubin’s rules. Imputation diagnostics include convergence trace plots and comparisons of observed versus imputed variable distributions. A complete-case sensitivity analysis is pre-specified (Table 3, sensitivity analysis #15). For follow-up data potentially deviating from the missing-at-random assumption, pattern-mixture models and tipping-point analyses are pre-specified.

Cumulative incidence functions are reported alongside cause-specific hazard analyses. Pre-specified sensitivity analyses are detailed in Table 3. Component-separate analyses of the functional improvement component (excluding the revascularization criterion) and the revascularization-free survival component are designated as mandatory pre-specified secondary analyses (Table 3), not optional sensitivity analyses; these analyses isolate each failure mode and will be reported in the primary publication regardless of the primary composite outcome results.

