The composite primary endpoint is designed to capture the two clinically relevant failure modes of SET: failure to achieve meaningful functional improvement and progression to revascularization before completing the program. Functional improvement thresholds are anchored to absolute improvement benchmarks for treadmill-based SET documented in the 2019 AHA scientific statement on optimal exercise programs for PAD [19], representing the minimum criteria for a meaningful clinical response. Revascularization events are independently adjudicated and classified to facilitate sub-analyses restricted to guideline-concordant intervention decisions [4], addressing concerns that elective revascularization may be influenced by patient preference rather than objective clinical failure. The Fine–Gray competing risks model is employed for time-to-event analyses to appropriately account for the competing event of death in this elderly and comorbid population [30], thus avoiding biases that could arise from standard Cox regression in the presence of significant competing risks.

The statistical framework is calibrated to the explicit derivation role of this study. With an expected 40 treatment failures, inferential precision for model discrimination will be limited, and all conclusions will therefore be confined to the direction and magnitude of predictor associations [26, 27]. This study lacks the event volume necessary to establish validated, externally generalizable clinical decision thresholds, and any such interpretations would be premature. Bootstrap internal validation will estimate optimism-corrected model performance; however, internal validation cannot substitute for external replication in an independent cohort.

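### The mandatory component analyses are said to isolate each failure mode, but none takes programme non-completion, a main source of the planned failures, as its outcome

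*Protocol article*

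**What the plan says.** All references are to the protocol article.

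- **Primary outcome** lists three failure scenarios. The first is "i) program non-completion, defined as failure to attend the requisite number of SET sessions, regardless of functional outcome". The second is functional non-response among completers. The third is revascularisation within three months.
- **Statistical analysis** sets the component analyses: "Component-separate analyses of the functional improvement component (excluding the revascularization criterion) and the revascularization-free survival component are designated as mandatory". It then says that "these analyses isolate each failure mode and will be reported in the primary publication regardless of the primary composite outcome results". In Table 3 these are #4 and #5.
- **Discussion** describes the composite as "designed to capture the two clinically relevant failure modes of SET" and names functional failure and revascularisation. Non-completion is not among them.
- **Sample size** gives the origin of the failure rate: "Assuming a treatment failure rate of 40%, reflecting the program non-completion component of the 40–50% failure rate reported in real-world European SET series", together with a local audit of about 38%. It adds that "this 40% assumption captures both program non-completion and early revascularization combined, without separately modeling the functional non-response rate among completers".
- **Table 3 #12** repeats the analysis in participants with at least 30 of 36 sessions. It is a sensitivity analysis, without the mandatory reporting status of #4 and #5.
- **Introduction** frames the target as "patients lacking the biological substrate for aerobic adaptation".

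**The concern.** Two analyses, neither with non-completion as its outcome, cannot isolate three failure modes. The statement about the plan's own safeguard is therefore wrong, and the Discussion's count of two conflicts with the Primary outcome section's three.

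The gap matters because the sample-size reasoning draws the planned failures largely from the mode that is left out. If lower muscle density or higher VAT goes with dropping out and has no relation to walking gain, H1 or H2 can still be positive on the composite. The mandatory component results would not show directly that attendance was the source. The biological framing of the Introduction and Discussion would then invite a conclusion about adaptive capacity when the data had shown prediction of completion.

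**Working it through.** **1. The plan's own figures.** Evaluable participants: 40 / 0.40 = 100. Enrolment: 100 / 0.78 = 128.2, so 128 to within rounding (128 × 0.78 = 99.84). Events per variable: 40 / 5 = 8. These reproduce.

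**2. Share of planned failures due to non-completion.** The Sample size section gives no split, and it is unclear whether the audit's 38% is non-completion or overall failure. Three readings:
- 38% is the non-completion rate among 100 evaluable: 38 of 40 failures (95%), leaving 2 others.
- The whole 40% is non-completion: 40 of 40.
- The 22% attrition, which the text says includes protocol non-completion, removes non-completers before the 100 are counted: 0.38 × 128 ≈ 49 non-completers, less up to 0.22 × 128 ≈ 28, leaves about 21 of 40.

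The range is about 21 to 40 of 40. Even at the low end, non-completion is about half of the planned failures.

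**3. Which described analyses bear on the question.**

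| Analysis | Status | Separates attendance from walking response? |
|---|---|---|
| #4 functional improvement | mandatory | Only if non-completers are classified on measured MWD; their coding is not stated |
| #5 revascularisation-free survival | mandatory | No |
| #12 adherent subgroup | sensitivity | In part: removes non-completers, does not model non-completion |
| Change in MWD, with Spearman correlations | secondary | In part: not described as covariate-adjusted; completion is not an outcome |

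**4. Information in #12.** On the 38% reading there are 100 − 38 = 62 completers with 2 planned failures, or 2 / 5 = 0.4 events per variable. If 10–30% of the other 60 completers are functional non-responders (assumed), failures number 2 + 6 = 8 to 2 + 18 = 20. A null result in #12 would be weak evidence.

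**5. Illustration of misattribution.** The protocol's effect is an odds ratio of 2.0 per 10 HU, with no SD given.
- The approximation Φ(√(n p(1−p)) × ln 2 × SD/10 − 1.96), with n = 100 and p = 0.40, gives the stated 80% power at SD ≈ 8.25 HU: √24 × 0.693 × 0.825 = 2.80, and Φ(0.84) = 0.80. At SD 7 it gives 66%, at SD 10 92%.
- SD 8.25 implies 2^0.825 = 1.77 per SD.

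Simulation settings, all assumed: n = 100, five predictors, 38% non-completion, odds ratio 1.77 per SD on non-completion only, 10–20% functional non-response unrelated to the predictor, test at 0.025.

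| Analysis | Positive |
|---|---|
| Composite | 36–45% |
| #4, non-completers counted as failures | 40–50% |
| #4, measured MWD only | about 2% |
| Completers only | 1–2% |
| Composite, predictor with no effect at all | about 3% |

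So #4 either reproduces the attendance signal or removes it, depending on a coding rule that the article does not state. If muscle density is correlated with the other covariates, the composite figures are lower.

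**The case against.** Several points against this have force.

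- *The composite has two formal criteria, and the two mandatory analyses match them.* True. But the same section counts non-completion as failure whatever the walking result, so it is a route that neither criterion captures.
- *Predicting non-completion is within the declared aim.* This stands. The aim is composite treatment success, and the Abstract and Conclusion name non-completion openly. The Discussion also confines conclusions to direction and magnitude of association and disclaims causal inference. A composite result carried by attendance would be valid. It would need to be described as such.
- *Other analyses help.* Also true in part. The adherent subgroup, the separate analysis of non-adherers mentioned in the SET section, and the continuous MWD outcomes all bear on the question. A withdrawal visit records MWD for those who attend it. A reader might infer that nothing planned could reveal an attendance effect; the documents do not support that.
- *Thirty-eight of 40 is not in the text.* Correct. A reader might take it as the plan's own split, but it is one reading of an ambiguous sentence. Planning figures also cannot fix the observed mix, since functional non-response was not modelled.
- *The simulation shows no error rate.* Correct. A predictor of one component truly predicts the composite, so 36–45% is power under an assumed mechanism. Reading it as a false-positive rate, or applying 2.0 per SD in place of the protocol's 2.0 per 10 HU, would overstate the matter.
- *A table of failures by mode may sit in the analysis plan that is not shown.* It may, and its absence from the article is not counted as an error.

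**Conclusion.** The statement that the two mandatory analyses isolate each failure mode is wrong as written, and the Discussion's two modes contradict the Primary outcome section's three. This rests on the text alone.

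The omitted mode is a main basis of the 40% planning rate: about half to all of the 40 planned failures, depending on what the audit and attrition figures mean. A positive H1 or H2 could therefore be carried by non-completion, and the described analyses separate that from walking response only in part. The simulated 36–45% depends on an assumed SD, an assumed attendance-only mechanism and an assumed functional non-response rate, and serves only to show that the scenario is not remote.

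The consequence is a risk of misinterpretation. The primary endpoint, model and significance level are unaffected, and attendance is recorded for each participant, so the breakdown remains recoverable. The point should be fixed, but it does not invalidate the design.

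**What to change.** 1. In Statistical analysis and Table 3, add programme non-completion (yes/no, all participants, same five predictors, same attendance definition as the primary outcome) as a third mandatory component analysis.
2. State that #4 classifies non-completers on measured MWD and does not count them as failures by default.
3. Report #12 alongside the component analyses, with the number of failures by mode.
4. State in advance that an association carried by non-completion will be reported as prediction of completion and not of exercise adaptation.
5. Reconcile the Discussion's count of failure modes with the Primary outcome section.

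At the least, remove the claim that each failure mode is isolated.

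**Cost.** One more secondary model, with about 38 / 5 = 7.6 events per variable on the 38% reading, close to the primary model's 8 but still modest, and fewer on the low reading. No new data collection is needed. In #4, non-completers who do not attend the withdrawal visit will depend on the planned imputation. Enrolment is planned to begin in June 2026, so the change can be made before any outcome data exist.
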